**Fig. 1 fig1:**
[figure not shown]
Enrollment, randomization and follow-up protocol of the study CS: Cigarette Smoking, DLP: Dyslipidemia, HTN: Hypertension.

### Sample size calculation

3.9

Farkouh et al. [22] which studied pooled data obtained from large randomized trials display the success rate in controlling risk factors in CAD patients for secondary prevention through lifestyle modification and drug consumption.

To increase the success rate percentage of modifying the risk factors by at least 1.5 times, concerning significance level of α = 0.05, study power of 80% and 10% loss of samples, a sample size of 257, 538, and 772 were considered for DLP, HTN, and CS, respectively. The largest sample size of 772 which is related to CS was selected (772 × 2 = 1544). The calculation was performed by G-power software. The final results are reported in Table 3.

**Table 3 tbl3:** Success rates in controlling Dyslipidemia, Hypertension and smoking and calculated sample size.

Risk Factor	Success rate percentage in the control group	Success rate percentage in the intervention group	Sample size in each group counting 10% shedding of samples	The abundance of patients referred to the Tehran Heart Center
**Dyslipidemia**	0.2	0.3	257	0.72
**Hypertension**	0.11	0.165	538	0.47
**Cigarette smoking**	0.08	0.12	772	0.34

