### Statistical methods

3.12

Continuous variables will be presented through mean with the standard deviation (SD) for normally distributed variables or median with the interquartile range boundaries for skewed variables. Categorical variables will be presented as the frequency with percentage. To check the normality distribution of continuous variables, histograms will be applied along with the above descriptive quantities. Risk factors’ status will be measured at different time points to determine the final status at the end of certain time points. We will compare the prevalence of the controlled risk factors in time points of 0 (baseline), 3 and 6 months between intervention and control groups using x^2^ tests at each point. Multivariate logistic regression analysis will be used to determine the effect of the intervention on the control of risk factors at the end of 6 months. The effect will be reported as Odds Ratios with the corresponding 95% confidence interval. This will be a per-protocol approach. To perform the intention-to-treat method, participants will be analyzed according to the group they were allocated not the actual intervention they received. The missing values for subjects who were lost to follow-up or did not cooperate until the end of the study will be evaluated to see to what extent the missing data are completely random. If missing data do not violate the randomness assumption, they will be replaced using the multivariate missing imputation method. Otherwise, stratified analysis and sensitivity analysis for missing data will be considered. Finally, the size of the effect is measured and reported as a relative risk/risk ratio with a corresponding 95% confidence interval. The effect will be calculated and reported as a hazard ratio with the corresponding confidence interval.

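### The three sample sizes match a one-sided 5% test at 80% power; under the planned two-sided analysis the power at those sizes is about 70%

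*Protocol article*

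**What the plan says.** Section 3.9 sets out to detect a 1.5-fold rise in the success rate for each risk factor, and gives its terms and results as "concerning significance level of α = 0.05, study power of 80% and 10% loss of samples, a sample size of 257, 538, and 772". Table 3 gives the assumed control and intervention rates: 0.20 and 0.30 for dyslipidaemia, 0.11 and 0.165 for hypertension, 0.08 and 0.12 for smoking. The three sizes are for these factors in that order, per arm and with the 10% loss included. The smoking figure fixes the trial: "The largest sample size of 772 which is related to CS was selected (772 × 2 = 1544"). G-power is named as the software. The sidedness of α is not given.

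Section 3.12 plans chi-square tests between arms at baseline, 3 and 6 months, and a logistic regression at 6 months: "The effect will be reported as Odds Ratios with the corresponding 95% confidence interval". A risk ratio with a 95% interval is also planned. Neither section mentions a one-sided test.

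**The concern.** A bare α of 0.05 in a plan that uses chi-square tests and 95% intervals will be read as two-sided. On that reading the printed sizes are too small for the rates in Table 3. If the calculation was run one-sided, the 80% belongs to a different test from the one the trial will perform. The chance of missing the assumed effect would then be about 30% rather than 20%, in the comparison that fixed the size of the trial. Readers of a null result would also be told that the study was better powered than it was.

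**Working it through.** **Inputs.** Rates p1 (control) and p2 (intervention) from Table 3; α = 0.05, power 80% and loss 10% from section 3.9; 1:1 allocation from section 3.10.

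**Formula.** Evaluable n per arm, pooled variance under the null, no continuity correction:

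n = [z_α·√(2·p̄·(1−p̄)) + 0.8416·√(p1(1−p1) + p2(1−p2))]² / (p2−p1)²

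where p̄ = (p1+p2)/2. The number to randomise is n/0.9.

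**Step 1: reproduce the printed sizes, one-sided (z_α = 1.645).**

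For smoking, p̄ = 0.10, √(2·0.10·0.90) = 0.4243 and √(0.08·0.92 + 0.12·0.88) = 0.4233. The numerator before squaring is 1.6449·0.4243 + 0.8416·0.4233 = 1.0541, so n = (1.0541/0.04)² = 694.5 and n/0.9 = 771.7.

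| Risk factor | n evaluable | n/0.9 | Rounded up | Table 3 |
|---|---|---|---|---|
| Dyslipidaemia | 230.8 | 256.4 | 257 | 257 |
| Hypertension | 483.7 | 537.5 | 538 | 538 |
| Smoking | 694.5 | 771.7 | 772 | 772 |

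One formula and one rounding rule reproduce all three rows. If n is rounded up to 695 before inflation, smoking gives 772.2, which is 772 to the nearest whole number or 773 rounded up.

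**Step 2: the same inputs, two-sided (z_α = 1.960).**

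For smoking: 1.960·0.4243 + 0.8416·0.4233 = 1.1878, so n = (1.1878/0.04)² = 881.8 and n/0.9 = 979.8.

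| Risk factor | n evaluable, rounded up | n/0.9, rounded up | Table 3 | Ratio |
|---|---|---|---|---|
| Dyslipidaemia | 294 | 327 | 257 | 1.27 |
| Hypertension | 615 | 684 | 538 | 1.27 |
| Smoking | 882 | 980 | 772 | 1.27 |

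Rounding only at the end gives 326, 683 and 980. Other two-sided 5%, 80% variants do not reach the printed figures either:

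- unpooled variance: 324, 680, 978
- arcsine: 325, 678, 973
- continuity-corrected: 348, 724, 1036
- pooled variance with loss added as n × 1.1: 324, 677, 971

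**Step 3: two-sided power at the printed sizes.**

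Power = Φ{[(p2−p1)·√n − 1.960·√(2·p̄·(1−p̄))] / √(p1(1−p1) + p2(1−p2))}

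For smoking with 695 evaluable per arm: (0.04·√695 − 1.960·0.4243)/0.4233 = 0.527, and Φ(0.527) = 0.701.

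| Risk factor | After 10% loss | Power | No loss | Power |
|---|---|---|---|---|
| Dyslipidaemia | 231 | 70.0% | 257 | 74.6% |
| Hypertension | 484 | 70.1% | 538 | 74.6% |
| Smoking | 695 | 70.1% | 772 | 74.6% |

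**Step 4: effect on the total.** Two-sided 80% power for smoking needs 980 × 2 = 1960 participants, against 1544 planned: 416 more.

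**The case against.** The strongest objection is that 70% is not the power of the trial as it will be run. All three factors share the largest size. If every participant had the factor in question, 695 evaluable per arm would give two-sided power of about 99% for dyslipidaemia and 85% for hypertension. Conversely, entry requires only one uncontrolled risk factor, so many participants will not smoke. If the Table 3 shares of 0.72, 0.47 and 0.34 held among those enrolled, which is an assumption, two-sided power would be about 96%, 53% and 30%. This stands as a limit on what the 70% describes: it belongs to each row of Table 3 at its own size. It does not rescue the calculation, because smoking set the total and 70% is its best case under the planned loss. The share of smokers is a separate and larger problem.

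Second, one-sidedness is inferred, not stated. A two-sided 5% test at 70% power also gives 257, 538 and 772. That is true, but this reading contradicts the stated 80% outright and leads to the same conclusion.

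Third, section 3.9 words its aim as an increase, and a fuller document might declare a one-sided design. Silence on sidedness in a condensed article would not by itself be a fault. The printed figures, however, do not fit the analysis that the same article describes.

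Finally, the mismatch neither biases the estimate nor inflates the type I error of the two-sided analysis. The error lies in the power claim and in the size derived from it.

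**Conclusion.** The concern holds. At the stated 80% power, the sizes in Table 3 are those of a one-sided 5% test, while the described analysis is two-sided at 5%. For that analysis each printed size gives about 70% power after the planned loss, or about 75% with complete retention, and each would need to be about 27% larger to reach 80%. The result rests on the Table 3 rates, the 10% loss, equal allocation and the uncorrected pooled test. The smoking figure also assumes that all 772 per arm are smokers. That α was entered as one-sided is a strong inference from the match in all three rows. The shortfall under a two-sided test does not depend on that inference.

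**What to change.** Check the G-power settings. Then, in section 3.9 and Table 3, state that 257, 538 and 772 correspond to a one-sided 5% test at 80% power, and that the power at those sizes under the planned two-sided 5% analysis is about 70% after 10% loss. Alternatively, print the two-sided sizes of 327, 684 and 980 beside the fixed total. Make clear that these figures refer to participants who have the risk factor in question, so that 70% is not read as the power of the whole trial.

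Keep the analysis two-sided. Moving to a one-sided test now would recover 80% only by relaxing the error standard.

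The cost is a sentence and a corrected table, with the stated power falling from 80% to about 70%. If the sponsor wishes to keep 80% two-sided for smoking on these inputs, the total rises from 1544 to 1960, still on the assumption that every participant smokes.

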▪ History of coronary artery disease^a^ ▪ Having at least one uncontrolled risk factor^b^ ▪ Aged between 25 and 75 years ▪ Inclination to stay in the study for 6 months ▪ The participant's (or one of their trustworthy relatives who live with them) having and ability to use a smartphone ▪ Willing to control the risk factors using an application ▪ Provides informed consent to participate in the study	• Mental retardation • Individuals with prohibitive morbidities that require close face-to-face monitoring. • End-stage chronic disease such as hepatic and/or renal failure, heart failure, active cancer

a History of myocardial infarction, percutaneous coronary intervention, coronary artery bypass graft surgery, coronary angiography confirming stenosis>50% in at least one of the major epicardial coronary arteries or their main branches.

b Including uncontrolled hypertension, uncontrolled dyslipidemia, and current cigarette smoking for ≥12 months.

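### The 1544 total counts 772 smokers per arm as 772 patients per arm, so the stated 80% power is not delivered for smoking or hypertension

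*Protocol article*

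**What the plan says.** Section 3.9 (Sample size calculation) aims "To increase the success rate percentage of modifying the risk factors by at least 1.5 times", with "significance level of α = 0.05, study power of 80% and 10% loss of samples". Table 3 turns this into three separate two-group comparisons:

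| Risk factor | Control rate | Intervention rate | n per arm, with 10% loss | Share of referred patients |
|---|---|---|---|---|
| Dyslipidemia | 0.20 | 0.30 | 257 | 0.72 |
| Hypertension | 0.11 | 0.165 | 538 | 0.47 |
| Smoking | 0.08 | 0.12 | 772 | 0.34 |

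The last column is headed "The abundance of patients referred to the Tehran Heart Center". The total then follows from the smoking row alone: "The largest sample size of 772 which is related to CS was selected (772 × 2 = 1544").

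Table 1 sets the risk-factor entry criterion as "Having at least one uncontrolled risk factor". Section 3.8 applies that criterion to all 1544. Section 3.10 lists seven randomization strata, three of which contain no smokers (hypertension only, dyslipidemia only, and the two together). The text sets no quota or enrichment for smokers.

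Section 3.6 makes the number of controlled risk factors (none to three) the primary outcome. Control of each single factor is a secondary outcome.

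**The concern.** A quit rate of 8% or 12% has smokers as its denominator, so 772 per arm is a count of smokers. Section 3.9 uses it as a count of all patients. The same applies to hypertension: 772 mixed patients per arm need not include the 538 hypertensive patients that Table 3 asks for. The shares needed for the conversion stand in the same table but are not used.

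A reader of section 3.9 will believe the trial has at least 80% power for each risk factor because it was sized on the most demanding one. If the true power for smoking is far lower, a real 1.5-fold gain in quitting would usually be missed, and the null result could be read as failure of the app. The only power statement in the article would also not support the sample size it is meant to justify, because the primary outcome has no calculation.

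**Working it through.** **Step 1: reproduce the plan's figures.** For two proportions with pooled variance under the null and no continuity correction:

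n = [z(α)·√(2p̄(1−p̄)) + z(0.80)·√(p1(1−p1) + p2(1−p2))]² / (p2−p1)², then divided by 0.9 for 10% loss.

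| Factor | One-sided 5%: n, then n/0.9 | Two-sided 5%: n, then n/0.9 | Stated |
|---|---|---|---|
| Dyslipidemia | 231, 257 | 294, 327 | 257 |
| Hypertension | 484, 538 | 615, 684 | 538 |
| Smoking | 695, 772 | 882, 980 | 772 |

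The one-sided smoking figure is 694.5/0.9 = 771.7, which rounds to 772; rounding to 695 first gives 773. The stated sizes therefore match a one-sided 5% test. Section 3.12 plans chi-square tests and "Odds Ratios with the corresponding 95% confidence interval", which are two-sided. Both conventions are shown below.

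**Step 2: patients per arm with each factor, at the Table 3 shares.**

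- Smoking: 0.34 × 772 = 262; × 0.9 = 236 evaluable.
- Hypertension: 0.47 × 772 = 363; × 0.9 = 327 evaluable.
- Dyslipidemia: 0.72 × 772 = 556; × 0.9 = 500 evaluable.

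**Step 3: power.** Power = Φ{[(p2−p1)·√n − z(α)·√(2p̄(1−p̄))] / √(p1(1−p1) + p2(1−p2))}.

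For smoking, n = 236 and p̄ = 0.10:

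- Two-sided: (0.615 − 0.832)/0.423 = −0.51, so power is 30%.
- One-sided: (0.615 − 0.698)/0.423 = −0.20, so power is 42%.

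**Step 4: allow for the entry criterion.** The shares describe referred patients, and only those with at least one factor can enrol, so shares among the enrolled may be higher. Two assumptions bracket this:

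- Independent factors: P(any factor) = 1 − 0.28 × 0.53 × 0.66 = 0.902.
- Maximal overlap (every smoker and hypertensive patient also has dyslipidemia): P(any factor) = 0.72.

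Dividing the Table 3 shares by these values gives:

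| Assumption | Smoking: share, per arm, power two-/one-sided | Hypertension: share, per arm, power two-/one-sided |
|---|---|---|
| Table 3 as printed | 34%, 262, 30%/42% | 47%, 363, 53%/65% |
| Independent factors | 38%, 291, 33%/45% | 52%, 402, 58%/69% |
| Maximal overlap | 47%, 365, 40%/53% | 65%, 504, 67%/78% |

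Dyslipidemia has 96% two-sided power even at its printed share.

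**Step 5: what the stated targets would need.**

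- 772 smokers per arm at a 34% share: 1544/0.34 ≈ 4,540 patients in total.
- 538 hypertensive patients per arm at 47%: 1076/0.47 ≈ 2,290.
- On the two-sided sizes (980 and 684 per arm), the totals are about 5,766 and 2,912.
- With 1544 patients, the smoking target is met only if everyone smokes. The hypertension target needs a share of 538/772 = 70%.

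**Step 6: the primary outcome.** Assume Table 3 rates and shares, independence of factors and of their control, and 772 × 0.9 ≈ 695 evaluable per arm. The proportions with 0, 1, 2 and 3 controlled factors are then about 76.7%, 21.9%, 1.3% and 0.02% in control, and 66.0%, 30.9%, 3.0% and 0.08% in intervention. A four-category chi-square test (3 degrees of freedom, noncentrality 20.5) has about 98% power. Comparing the proportion with at least one controlled factor (23.3% vs 34.0%) gives about 99%.

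**The case against.** The strongest reply has four parts.

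- **The shares are not those of the enrolled.** Table 3 describes referred patients, and it does not say whether it counts uncontrolled factors or any history. This is a fair limit on precision, and it is why a range is given. It does not rescue smoking: even at maximal overlap there are 365 smokers per arm, under half of 772. Hypertension is the closer case, with 504 against 538 and 78% one-sided power at best. If the 47% includes controlled hypertension, the true share is lower and the shortfall larger.
- **Two problems are mixed.** Because the stated sizes match a one-sided test, part of the fall to 30% comes from sidedness. With all 772 per arm smoking, two-sided power after 10% loss would be only 70%. This is right, and the like-for-like loss from the smoker share alone is from 80% to 42%. The conclusion is the same under either convention, and the two-sided figures are those that fit the planned analysis.
- **Single-factor outcomes are secondary.** True, and the primary comparison appears well powered. But the single-factor comparisons are the only ones for which the article states power, and smoking is the given reason for 1544.
- **Figure 1 is not available here.** It could in principle show a quota. The text of sections 3.8 to 3.10 states none.

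**Conclusion.** The concern holds. Section 3.9 treats a requirement for smokers as a requirement for patients, and the stated 80% is missed for smoking and hypertension in every case examined.

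Smoking is severely short: 30% to 40% two-sided power, or 42% to 53% one-sided. Hypertension is short by less: 53% to 67% two-sided, or 65% to 78% one-sided. Dyslipidemia is not affected.

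These figures rest on the Table 3 rates and 10% loss, on enrolment that follows the referral mix without enrichment, and on the range of overlap described. The primary comparison is not shown to be underpowered; its roughly 98% power depends on the independence assumptions. What must be corrected is the stated justification for the sample size and the power claimed for two of the three risk factors.

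**What to change.** Keep 1544 and rewrite section 3.9 and Table 3:

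1. Remove the statement that the total was chosen to power the smoking comparison.
2. Base the stated power on the primary outcome at 6 months. Name the test, its sidedness, and the assumed rates, shares and overlap. Give the power over a range of assumptions, since the 98% above is conditional on independence. The top category is almost empty under these assumptions, so state how sparse categories are handled.
3. Report the expected numbers per arm before loss, about 260 to 365 smokers and 360 to 500 hypertensive patients, with two-sided power of 30% to 40% and 53% to 67%.
4. Describe the smoking and hypertension comparisons as secondary and focused on estimation, so that a wide interval is not read as absence of effect.
5. State whether the Table 3 shares refer to uncontrolled factors or to any history.

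The cost is a text and table revision with no added patients or procedures. The stated power for smoking and hypertension becomes less favourable.

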### Randomization and implementation

3.10

Randomization will be performed at 7 different levels based on the type and number of risk factors the patients have (stratified randomization). Participants will be categorized into the following 7 levels; 1) Only CS, 2) Only HTN, 3) Only DLP, 4) CS + HTN, 5) CS + DLP, 6) DLP + HTN, 7) CS + HTN + DLP.

Participants in each level will be randomized into two study arms as follows.1Intervention (case) arm: Usual care + mHealth2Control arm: Usual care + paper-based recommendations and educational materials

In each level, participants will be assigned into two arms by block randomization with a 1:1 allocation using variable block sizes of 2, 4, 6, 8, and 10. Allocation of each subject to the study arms will be performed online to prevent selection bias and respect allocation sequence concealment (By concealing the allocation sequence). Allocation of each participant will be performed, just after inclusion and exclusion criteria are met and informed consent is signed by the participants. Computer-generated random number list will be utilized using permuted block stratified randomization. (Block stratified randomization Windows Version 6.0, by Steven Piantadosi, M. D., Ph.D., Cedars-Sinai Medical Center).

The practitioners who evaluate the risk factors controlling status are blinded to the group assignment.

#### Pilot study descriptions for mHealth app

3.10.1

After the development of the app, we will conduct a pilot study to evaluate the feasibility and acceptability of the app among a small sample group of volunteers in our center. The objective of this phase is to refine the design and development and pilot testing of the app. The potential participants will be recruited from THC outpatient clinics. Feasibility will be assessed by examining the participant's interactions with the app via backend reporting tools. Acceptability will be examined during follow-up visits or phone calls to examine satisfaction with the application in terms of ease of use and effectiveness. Following the pilot study, we will implement the required changes and refinements to the app before testing its efficacy in a randomized controlled trial in a larger study.

### Data collection and statistical analysis

3.11

We are going to record all the patient's demographic and clinical characteristics.

(Including past medical history, duration of each disease, drug and habitual history, etc.) and status of their risk factors (controlled/uncontrolled). BP, height, weight, and waist circumference will be measured during each visit. The blood sample will be taken before each visit to measure the serum level of the following factors: Creatinine, LDL-C, Glycated hemoglobin (HbA1C), Total cholesterol, High-density lipoprotein (HDL-C), Fasting blood glucose (FBS) and Triglyceride. In addition, we will request all the patients to present every laboratory test report that was done even outside THC and all other documents related to any event that required hospitalization within the last year. Hypertensive patients in the control arm will receive a paper-based chart to document their BP (systolic and diastolic) for 7 consecutive days in each month (the intervention group will also enter and save the measurements in the app).

The data will be collected from a paper questionnaire which is filled out by the research team and saved information on the digital server. Data entry will be conducted on the IBM SPSS software database.

### Statistical methods

3.12

Continuous variables will be presented through mean with the standard deviation (SD) for normally distributed variables or median with the interquartile range boundaries for skewed variables. Categorical variables will be presented as the frequency with percentage. To check the normality distribution of continuous variables, histograms will be applied along with the above descriptive quantities. Risk factors’ status will be measured at different time points to determine the final status at the end of certain time points. We will compare the prevalence of the controlled risk factors in time points of 0 (baseline), 3 and 6 months between intervention and control groups using x^2^ tests at each point. Multivariate logistic regression analysis will be used to determine the effect of the intervention on the control of risk factors at the end of 6 months. The effect will be reported as Odds Ratios with the corresponding 95% confidence interval. This will be a per-protocol approach. To perform the intention-to-treat method, participants will be analyzed according to the group they were allocated not the actual intervention they received. The missing values for subjects who were lost to follow-up or did not cooperate until the end of the study will be evaluated to see to what extent the missing data are completely random. If missing data do not violate the randomness assumption, they will be replaced using the multivariate missing imputation method. Otherwise, stratified analysis and sensitivity analysis for missing data will be considered. Finally, the size of the effect is measured and reported as a relative risk/risk ratio with a corresponding 95% confidence interval. The effect will be calculated and reported as a hazard ratio with the corresponding confidence interval.

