### Definitions

3.7

•**Current cigarette smoker:** Average of ≥5 cigarettes daily use in at least the year before enrollment.•**Successful smoking cessation:** Continuous abstinence in at least 4 weeks during 6 months following up.•**Uncontrolled DLP:** Description for uncontrolled DLP will be based on the serum level of LDL-C which depends on the concomitant comorbidities including diabetes mellitus and CVD [18]. The related cut-off value for the serum level of target LDL-C is ≤ 55 mg/dL. Values more than the listed cut-off value are considered uncontrolled DLP.•**Controlled DLP**: Lowering serum level of LDL-C by < 55 mg/dL and ≥50% reduction from baseline in any of the follow-up visits at the end of 3 and 6 months from randomization and remaining controlled in the next visits during the study.•**Uncontrolled HTN:** A patient who has a history of HTN with/without using the antihypertensive drug is considered hypertensive. Participants will be considered as having uncontrolled HTN according to the ACC/AHA guidelines [19].•**Controlled HTN:** Maintaining BP below the target treatment level (130/80 mmHg) at the time of office measurements (average of 2 readings obtained on 2 separate occasions with proper patient preparation and appropriate technique) at the end of 3 and 6 months from randomization and/or during one-week daily home measurements (average of records) before clinic visits.

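### The primary 0–3 count and the section 3.12 comparison have no rule for a risk factor that the patient did not enter with

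*Protocol article*

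**What the plan says.** - **Entry (section 2.4, Table 1).** At least one uncontrolled factor out of hypertension (HTN), dyslipidaemia (DLP) and current cigarette smoking (CS).
- **Randomisation (section 3.10).** Seven levels: "1) Only CS, 2) Only HTN, 3) Only DLP, 4) CS + HTN, 5) CS + DLP, 6) DLP + HTN, 7) CS + HTN + DLP". Only the seventh contains all three factors.
- **Primary outcome (section 3.6).** A four-category count, from no controlled factor to three, at 3 and 6 months. It is not limited to the factors the patient entered with.
- **Secondary outcomes (section 3.6).** Control of single factors and of combinations, introduced as control within each stratification level.
- **Definitions (section 3.7).** Smoking success: "Continuous abstinence in at least 4 weeks during 6 months following up". Controlled HTN: "Maintaining BP below the target treatment level (130/80 mmHg) at the time of office measurements", and/or on averaged home readings. Controlled DLP: "Lowering serum level of LDL-C by < 55 mg/dL and ≥50% reduction from baseline".
- **Data (section 3.11).** Factor status is recorded as controlled or uncontrolled; no third category is named.
- **Analysis (section 3.12).** "We will compare the prevalence of the controlled risk factors in time points of 0 (baseline), 3 and 6 months between intervention and control groups", by chi-square test at each time, then a multivariable logistic regression at 6 months. No denominator, covariate list or stratification is given.

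**The concern.** A count of up to three factors is applied to patients who mostly entered with one or two. The definitions do not treat the missing ones alike. Blood pressure below target needs no hypertension at entry. Four weeks of abstinence could be read as met by a non-smoker. A patient who entered without uncontrolled LDL-C gets no such automatic credit, because a fall of at least 50% is required.

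Three scorings are therefore open for an absent factor: credit it, score it as not controlled, or leave it out of the denominator. If it is credited, much of what is reported as control was present before randomisation in both arms. The unadjusted ratio measures then shrink towards 1, and the count largely reflects which factors the patient brought to the trial. If the rule is not fixed in advance, the choice could be made after the results are known.

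**Working it through.** **Step 1: the plan's own figures.** Section 3.9 works "concerning significance level of α = 0.05, study power of 80% and 10% loss of samples". Inputs are the Table 3 success rates. Per arm, n = [z(α)·√(2p̄(1−p̄)) + 0.842·√(p1(1−p1)+p2(1−p2))]² / (p2−p1)², divided by 0.90 for loss.
- One-sided 5%: 231, 484 and 695 before loss; 257, 538 and 772 after loss (695/0.90 = 772.2). These match the plan for DLP, HTN and CS.
- Two-sided 5%: 327, 684 and 980 after loss. These do not match.

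The plan does not state sidedness. Two-sided 5% is used below. The 772 per arm is a number of smokers.

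**Step 2: share of patients with each factor.** Table 3 gives 0.72 (DLP), 0.47 (HTN) and 0.34 (CS) among referred patients. Assuming independence, the share with at least one factor is 1 − 0.28×0.53×0.66 = 0.902. Dividing by 0.902 gives f = 0.798 (DLP), 0.521 (HTN) and 0.377 (CS) among those enrolled.

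**Step 3: three scorings for the crude comparison.** With success rate p among patients who have the factor:
- own factor only: rate p, n = 772f per arm (CS 291, HTN 402)
- absent factor credited: rate (1−f) + f·p, n = 772
- absent factor scored not controlled: rate f·p, n = 772

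Power = Φ{[(p2−p1)√n − 1.96√(2p̄(1−p̄))] / √(p1(1−p1)+p2(1−p2))}.

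| Factor | Scoring | Control v intervention | RR | OR | Power |
|---|---|---|---|---|---|
| CS | own factor only | 8% v 12% | 1.50 | 1.57 | 36% |
| CS | credited | 65.3% v 66.8% | 1.02 | 1.07 | 9% |
| CS | not controlled | 3.0% v 4.5% | 1.50 | 1.52 | 34% |
| HTN | own factor only | 11% v 16.5% | 1.50 | 1.60 | 62% |
| HTN | credited | 53.6% v 56.5% | 1.05 | 1.12 | 20% |
| HTN | not controlled | 5.7% v 8.6% | 1.50 | 1.55 | 59% |

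Worked entry, CS credited: 0.623 + 0.377×0.08 = 0.653 and 0.623 + 0.377×0.12 = 0.668. Power = Φ[(0.0151×27.78 − 1.96×0.6695)/0.6695] = Φ(−1.33) = 0.09. DLP is not credited automatically, because of the 50% fall.

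**Step 4: the count.** Own factors only, the control-arm mean is 0.377×0.08 + 0.521×0.11 + 0.798×0.20 = 0.247. The intervention mean is 1.5 times that, 0.371, a difference of 0.124. Crediting absent CS and HTN adds 0.623 + 0.479 = 1.102 to both means, giving 1.349 v 1.473, again a difference of 0.124. Enumerating the seven levels with independent outcomes, the control-arm share with two or three controlled factors rises from about 1% to about 41%. For the count itself, leaving an absent factor out and scoring it zero give the same number; only crediting changes it.

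**Step 5: adjustment for level.** If everyone in a level without smoking is scored as controlled for smoking, that level carries no information on the smoking odds ratio. A level-adjusted model then rests on the levels with smokers and returns about 1.57.

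**Step 6: sensitivity.** With unadjusted Table 3 shares and 695 evaluable per arm, crediting gives RR 1.02 (power 8%, against 30% in smokers only) and RR 1.04 (power 16%, against 53% in hypertensives only). Smoking shares of 25% to 50% give RR 1.01 to 1.04. Hypertension shares of 35% to 60% give RR 1.03 to 1.07.

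**The case against.** The strongest reply is that the crediting reading ignores context. The smoking definition is headed as cessation, and someone who does not smoke cannot cease. The blood-pressure definition speaks of a treatment target and follows a sentence on who counts as hypertensive; sections 3.1 and 3.11 set up home charts for hypertensive patients. Section 3.6 ties the secondary outcomes to the stratification levels, and their list mirrors those levels. The text is also a condensed article, and analysis sets are often left to the analysis plan.

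Much of this stands. The single-factor secondary outcomes have an implied denominator, and the label argues against crediting non-smokers. But the stratum wording does not reach the primary count or the section 3.12 comparison. The blood-pressure wording remains open to patients who entered without uncontrolled hypertension. The article itself sets out the outcome categories, the definitions and the tests, and these do not fit together.

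A reader might also infer from the planned test at time 0 that all patients are meant to be scored, since control of an entry factor is zero then by design. The documents do not support that. The lipid definition needs a fall from baseline and the smoking definition needs abstinence during follow-up, so nobody can meet either at time 0 under any scoring. A patient with known, already controlled hypertension who entered for another factor could give the test some content without any crediting. The time-0 test is uninformative for entry factors, but it does not show which scoring is intended.

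**Conclusion.** The point holds as a gap and an inconsistency in the primary count and in the section 3.12 comparison. It should be closed before outcomes are compared by arm.

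The dilution figures are an upper bound for the crude comparison under one of three readings. They assume that every patient without the factor is scored as controlled throughout, that factors and outcomes are independent, that Table 3 referral shares apply to those enrolled, and that all 772 per arm are evaluable. Scoring absent factors as not controlled keeps the risk ratio at 1.5 and costs little power. The absolute difference in the mean count is the same under all the scorings. Adjustment for level would recover much of the loss.

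A reader might go further and conclude that the plan does credit non-smokers and normotensive patients, or that the treatment effect will be swamped. The documents do not say the first. The second applies only to an unadjusted analysis under that reading. The low power among smokers alone (36%) is a separate matter, which comes from applying a number of smokers to a mixed sample; settling the scoring rule does not cure it.

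**What to change.** In sections 3.6, 3.7 and 3.12, state that:
- each factor is scored only in patients randomised in a level that contains it (four of the seven levels for each factor);
- the primary count covers only the factors the patient entered with;
- the primary comparison is stratified by, or adjusted for, the seven randomisation levels, since the highest possible count depends on the level.

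Replace the time-0 chi-square test of controlled status with a descriptive baseline table by arm, for example LDL-C, blood pressure and cigarettes per day.

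The cost is wording only: no new data, visits or patients. The downside is a different denominator for each factor, but it is fixed in advance by randomisation level.
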